## Abstract

**Background:**

Although morbidity and mortality from coronary heart disease (CHD) are high, only a minority of acute coronary syndrome (ACS) survivors accesses an effective secondary prevention program. We aim to determine whether the previously proven CHOICE program can be replicated at multiple sites and whether ongoing reinforcement further improves risk factor modification.

**Methods/design:**

Participants eligible for but not accessing standard cardiac rehabilitation will be randomly allocated to either a previously tested 3-month CHOICE program or a 30-month CHOICE program (CHOICE-*plus*). Both groups will participate in individualised risk factor modules of differing duration that involve choice, goal setting and telephone follow-up for three months. CHOICE-*plus *will also receive additional face-to-face and telephone reinforcement between three and 30 months. At one site we will recruit a randomised control group, receiving conventional care. Primary outcomes are lipid levels, blood pressure, physical activity levels and smoking rates. Secondary outcomes include readmission rates, death, the number of risk factors, other modifiable risk factors, quality of life and process evaluation measures over three years.

**Discussion:**

We present the rationale and design of a multi-centre, replication study testing a modular approach for the secondary prevention of CHD following an ACS.

**Trial Registration:**

[Clinical Trial Registration Number, ACTRN12608000182392]

## Background

Coronary heart disease (CHD) is a leading cause of death and disability in Australia and costs associated with treatment are high [1]. Survivors of an acute coronary syndrome (ACS) have a 5% risk of a recurrence, some six times greater than that of the general population [2] and are advised to participate in a secondary prevention program [3,4]. Such programs incorporate lifestyle advice and pharmacotherapy to reduce recurrent cardiovascular events, improve survival and enhance quality of life [4]. The population is aging and thus the prevalence of CHD is expected to increase [5]. Similarly, the number of people surviving an ACS is rising largely due to improvements in acute treatment [6,7]. Because of these increases, the need to provide effective secondary prevention programs is escalating. In addition, three recent large studies concluded that effective risk factor reduction has reduced mortality from CVD by around 50% [6-8].

Cardiac rehabilitation (CR) programs aim to reduce coronary risk factors, facilitate patients return to normal activities and reduce their overall cardiovascular risk, in addition to stabilising, slowing or even reversing the underlying atherosclerotic process [9,10]. However, despite the potential benefits of CR, only a minority of people with CHD (10–30%) participate in existing programs [11,12]. Reasons for poor attendance include geographical location, being of lower socio-economic group and low referral rates for the elderly and women [13]. In addition, even in those who attend, long-term compliance with exercise-only CR regimens is only around 50% [13].

Disconcertingly, the majority of ACS survivors, who are at high risk of a future cardiac event, do not access a formal secondary prevention program resulting in a significant evidence-practice gap. In a single-centre study, it was demonstrated that ACS survivors not accessing CR had higher levels of individual risk factors including elevated total cholesterol (TC), low density lipoprotein (LDL) cholesterol, current smokers, hypertension, overweight, are less physically active, and were therefore at much greater overall risk than CR attendees [14]. Non-CR attendees also had much poorer knowledge of their risk factors, where 75% were unable to state even one of their own risk factors [14].

CHD is a chronic condition, and changes to lifestyle and adherence to pharmacotherapy have to be life-long. Studies have tried to address this evidence-practice gap through education and counselling of risk factor targets and medications with success [15,16]. Using a simple, innovative patient-centred modular approach to secondary prevention in a randomised controlled trial (n = 208) [17,18], it was found that the Choice of Health Options In prevention of Cardiovascular Events (CHOICE) program was readily acceptable to ACS survivors who did not access standard CR. It was also found that the intervention group significantly reduced individual cardiovascular risk factors and overall risk, and had significantly better risk factor knowledge at both three and 12 month follow-up compared to baseline and compared to having conventional care with their usual general practitioner and/or cardiologist [19-21]. Therefore, it was demonstrated at a single hospital site that the evidence-practice gap could be reduced for up to 12 months.

The original CHOICE trial provided a successful secondary prevention option for patients not accessing CR at a single site but it is now imperative to determine if the findings are replicable at multiple sites, delivered by multiple health professionals and to examine the processes which influence the implementation of a successful trial into a "real-life" setting [22]. The aim of this study is to establish if the CHOICE program can be replicated at multiple hospitals over three years. We also aim to investigate whether 30 months of telephone support is more beneficial than three months.

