## Methods/design

### Design

This replication study, with a single site randomised control group, with three year follow up will be conducted at four tertiary referral hospitals in Sydney, Australia (figure 1) and is registered on the Australian and New Zealand Clinical Trials Registry (ACTRN12608000182392). Across all four sites patients not accessing standard CR will be randomly allocated to either a group participating in a three month CHOICE program or a 30 month CHOICE program (CHOICE-*plus*). At one site, patients not accessing CR will be allocated to one of three groups; the previously described intervention groups or a randomised control group participating in conventional care (figure 1), which will allow investigation of the effect of an additional nutrition module and a more tailored approach to depression.

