### Statistical analysis

Primary analyses will be conducted by intention-to-treat using SPSS for Windows (Version 12.01) and will be presented as mean and standard error of the mean or proportions. Differences in outcome measures, between and within groups, will be compared using repeated measures ANOVAs for continuous variables and either χ^2 ^tests or Fishers exact tests, as appropriate, for proportions of categorical variables. Two tailed p values of < 0.05 will be considered significant. Number needed to treat will also be calculated to estimate the number of patients who need to receive the CHOICE intervention to lower each of the major risk factors (TC, LDL-cholesterol, BP, smoking cessation, physical activity and overweight) to below current national targets.

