## Discussion

The findings of this replication study could have wide-ranging implications for the management of patients with CHD who are at highest risk of adverse events, namely survivors of an ACS. We anticipate this study will demonstrate that the large evidence-practice gap for the many ACS survivors not accessing CR can be narrowed by a brief, flexible and tailored modular intervention (CHOICE) to change behavior, reduce overall cardiac risk, and thereby reduce the likelihood of death, infarction, and recurrent symptoms. By demonstrating the generalisability of the previously proven CHOICE program, this approach, using existing personnel and community resources could easily be adopted state-wide at relatively low cost.

The ultimate goal for our patients is to maintain behavioural change and risk factor reduction in the long term within their local community. At the conclusion of this study we anticipate that we will be able to determine whether ongoing reinforcement is important to lower risk, and if this strategy can be implemented at multiple sites and consequently narrow the evidence-practice gap in the longer term.

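### The lead aim is multi-hospital replication of a result against conventional care, but only one of four sites has a randomised control group, so the anticipated multi-site effectiveness conclusion is not supported

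*Protocol article*

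**What the plan says.** The Background section argues that "it is now imperative to determine if the findings are replicable at multiple sites" and gives the lead aim as "The aim of this study is to establish if the CHOICE program can be replicated at multiple hospitals over three years". It describes the original single-site findings as lower risk factors and better risk-factor knowledge, "compared to baseline and compared to having conventional care with their usual general practitioner and/or cardiologist". Superiority over conventional care is therefore part of what is to be replicated.

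The Design section calls the trial "This replication study, with a single site randomised control group" and adds: "At one site, patients not accessing CR will be allocated to one of three groups". The purpose it gives for that three-arm site is "which will allow investigation of the effect of an additional nutrition module and a more tailored approach to depression". Group allocation confirms that the other three sites randomise only between CHOICE and CHOICE-plus. It places the baseline assessment during the inpatient stay or within one month of discharge.

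Statistical analysis states: "Differences in outcome measures, between and within groups, will be compared", by repeated measures ANOVA for continuous outcomes and chi-squared or Fisher tests for proportions, at two-sided 0.05. It also plans a number needed to treat for receiving CHOICE. It gives no criterion for successful replication.

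The Discussion expects the trial to show that CHOICE narrows the evidence-practice gap, lowers cardiac risk and so makes death and infarction less likely. It then argues for state-wide adoption, "By demonstrating the generalisability of the previously proven CHOICE program".

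**The concern.** To show at several hospitals that CHOICE works better than conventional care, the trial needs a conventional-care comparator at several hospitals. Three of the four have none. Randomising three months against 30 months there shows whether reinforcement adds anything. It cannot show whether either programme beats conventional care, because everyone receives CHOICE.

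That leaves change from baseline as the only outcome evidence about CHOICE itself at those sites. The start point is soon after an acute coronary event, when improvement can be expected without any programme. Significant within-group results at four hospitals could then be presented as replication, and used to argue for state-wide adoption, whether or not the programme had an effect.

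**Working it through.** **1. What each source of evidence can show**

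| Evidence | Sites | Randomised | What it estimates |
|---|---|---|---|
| CHOICE or CHOICE-plus against control | 1 of 4 | Yes | Effect against conventional care, at that site |
| CHOICE-plus against CHOICE | 4 of 4 | Yes | Added value of reinforcement |
| Within-group change | 4 of 4 | No | Programme effect plus everything else that changes after the event |
| Process and fidelity measures (Outcome measures section) | 4 of 4 | No | Delivery, uptake, barriers |

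No row gives an effect against conventional care at more than one hospital.

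**2. The protocol's own sample-size figures**

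- Inputs (Sample size section): two-sided 0.05, 80% power, 0.35 SD = 0.35 mmol/L. The SD of total cholesterol is therefore taken as 1.0 mmol/L.
- CHOICE against CHOICE-plus: n = 2 × (1.960 + 0.842)² / 0.35² = 2 × 7.849 / 0.1225 = 128.1, so 129 per group. The stated 138 gives about 83% power, which is slightly conservative.
- Control contrast: 64 controls, at the single site. No effect size is given. With 64 against 64, a t-test has 80.1% power for 0.50 SD and 96% for 0.66 SD. The earlier trial reported a difference of 0.66 mmol/L.

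Both randomised contrasts are adequately sized for what they estimate. The control contrast is sized as a one-site question.

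**3. How little background change makes a within-group test significant**

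- Inputs: 138 per group and SD 1.0 mmol/L, from the protocol. The correlation r between baseline and follow-up is not given, so 0.5 is assumed, with a range of 0.3 to 0.7.
- SD of change = √(2(1 − r)): 1.18 at r = 0.3, 1.00 at r = 0.5, 0.77 at r = 0.7.
- Change detected with 80% power = 2.80 × SD of change / √138, where √138 = 11.75.
- r = 0.5: 2.80 × 1.00 / 11.75 = 0.24 SD (0.24 mmol/L).
- r = 0.3: 2.80 × 1.18 / 11.75 = 0.28 SD.
- r = 0.7: 2.80 × 0.77 / 11.75 = 0.18 SD.

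At r = 0.5, a fall from causes other than the programme of 0.24 / 0.66 = 36% of the earlier between-group effect would give a significant within-group result four times in five with no programme effect. The protocol gives no estimate of the background change. This shows the test's sensitivity to it and does not forecast it.

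**4. Why background change is to be expected**

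Physical activity is a primary outcome, and its questionnaire covers the preceding seven days. For a patient assessed in hospital or shortly after discharge, that week can fall in the admission or early convalescence. Medication may change after the event. Patients counted as above a target at baseline will on average move towards it at remeasurement.

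**5. The number needed to treat**

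A number needed to treat is the reciprocal of a difference in proportions between treated and untreated patients. The only randomised untreated patients are at the three-arm site.

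**The case against.** The strongest reply is that replication here largely means implementation. The Outcome measures section says the generalisability of CHOICE will be evaluated by process measures: recruitment, withdrawal, context, resources, barriers and fidelity. The Background refers to delivery by several health professionals, and the Discussion closes by asking whether the strategy can be implemented at several sites. The single-site control group is disclosed openly. This stands, and it means that part of a suitable conclusion is already in the text. It does not cover the Discussion's claims about reduced risk and fewer events, or a Background that defines the earlier findings partly by superiority over conventional care.

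Three stronger readings are tempting, and the document does not support them.

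- *A within-group p-value decides replication.* The Statistical analysis section lists within-group comparisons but attaches no replication criterion to them. The concern is what those tests could be taken to show.
- *Controls from one site will be compared with CHOICE patients from all four, confounding arm with site.* No section says so, and Sample size places the control contrast at the single site. The absence of a site term is something an article may leave to the analysis plan. Any type I error attached to such pooling would need an assumed split of patients over sites, and would apply the intraclass correlation to levels although the trial is sized on change in total cholesterol.
- *The design is invalid without controls at every site.* Both randomised comparisons remain valid for their own questions. Where to place controls is a design trade-off, and the point does not depend on changing it.

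**Conclusion.** The point holds as a mismatch between the aim, the design and the anticipated conclusion. It should be fixed, but it does not invalidate the trial. The design supports a randomised effect against conventional care at one hospital, a randomised comparison of CHOICE-plus with CHOICE at four, and a description of delivery and fidelity at four. It does not support effectiveness against conventional care at multiple hospitals, and no analysis can create that comparison at three sites without controls.

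This conclusion rests only on where the control group is placed. The figure of 0.24 mmol/L (range 0.18 to 0.28) shows how easily a within-group test could mislead. It rests on the protocol's 138 per group and implied SD of 1.0 mmol/L, and on an assumed visit correlation of 0.3 to 0.7.

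**What to change.** 1. **Statistical analysis.** Report within-group changes by site, descriptively and with confidence intervals. State that within-group significance tests will not be used as evidence of effect or of replication.
2. **Statistical analysis.** State that effect claims against conventional care, including the number needed to treat, use only patients randomised at the three-arm site. This agrees with the Sample size section and makes it explicit.
3. **Background and Discussion.** Restate the aim and the anticipated conclusion. Randomised evidence against usual care comes from one site. Multi-site evidence covers CHOICE-plus against CHOICE, delivery and fidelity.

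All three are changes to wording and analysis. They need no extra patients, visits or sites. The cost is a more modest claim, in particular a weaker basis for arguing state-wide adoption on grounds of effect.

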## Methods/design

### Design

This replication study, with a single site randomised control group, with three year follow up will be conducted at four tertiary referral hospitals in Sydney, Australia (figure 1) and is registered on the Australian and New Zealand Clinical Trials Registry (ACTRN12608000182392). Across all four sites patients not accessing standard CR will be randomly allocated to either a group participating in a three month CHOICE program or a 30 month CHOICE program (CHOICE-*plus*). At one site, patients not accessing CR will be allocated to one of three groups; the previously described intervention groups or a randomised control group participating in conventional care (figure 1), which will allow investigation of the effect of an additional nutrition module and a more tailored approach to depression.

**Figure 1 F1:**
[figure not shown]
**Design of the CHOICE study**. ACS: acute coronary syndrome. CHOICE: Choice of Health Options In prevention of Cardiovascular Events.

Blinded assessments will be conducted at baseline and 36 months during a face-to-face interview. At 12 months, assessments will be completed by the intervention nurse and to ensure validity, a sample of 20 patients will have their measurements repeated by an independent assessor, blinded to group allocation. At follow-up assessments, additional data will be collected, including details of any unplanned hospital admissions, medications and doses and details of visits to the family physician, cardiologist and attendance at any community program pertaining to their heart health. Ethical approval for this study has been granted by Sydney South West Area Health Services and will be sought from the University of Sydney Human Research Ethics Committees. Written and informed consent will be obtained from all study participants prior to commencement.

### Study population

The hospital CR coordinators who review the Cardiology Department admission summaries daily will identify potential participants. Inclusion criteria for the study are; diagnosis of ACS up to eight weeks prior to recruitment; refusal of the initial invitation to participate in standard CR; failure to attend initial CR assessment. Exclusion criteria are: clinical diagnosis of uncompensated, severe cardiac failure (Class IV); uncontrolled arrhythmia or angina; severe or symptomatic aortic stenosis; persistent hypotension (SBP < 90 mmHg); clinical diagnosis of a severe coexisting medical condition that would prevent participation (e.g., dementia, a terminal illness, severe rheumatoid arthritis); or insufficient English to provide written informed consent. The primary criterion for eligibility for recruitment will be declining an offer to access existing CR. This will also include patients who are not offered CR while an inpatient but decline a subsequent offer to attend the CR program.

### Group allocation

Patients meeting the inclusion and exclusion criteria will be approached by the hospital CR coordinator or research assistant, during their inpatient stay where possible, or via letter or telephone soon after hospital discharge. Those who volunteer will have a baseline assessment and an initial face-to-face module selection and goal-setting session (approximately one hour in duration). This session will take place during the inpatient stay or in outpatient clinical consulting rooms, or, if necessary, at the participant's home, within one month of discharge. After baseline measurements are completed, at three sites, participants will be randomly allocated to one of the two groups (CHOICE or CHOICE-*plus*). At the remaining site participants will be randomly allocated to one of three groups (control, CHOICE or CHOICE-*plus*). Randomisation will be undertaken by an independent researcher (at the University of Sydney) with a computer-generated random allocation sequence and will be concealed from the health professional obtaining consent and conducting baseline assessment.

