### Interventions

Participants randomly allocated to the control group at the single site will participate in ongoing conventional care, aimed at managing their cardiovascular health as directed by their family physician, ideally in consultation with their cardiologist. The control group will be advised to seek the advice of their family physician and cardiologist but will receive no additional intervention as a result of participation in the study.

Participants in both the CHOICE and CHOICE-*plus *groups will take part in a three-month patient-centred modular secondary prevention program. The CHOICE-*plus *group will also be offered additional face-to-face reinforcement at 12 and additional telephone reinforcement at six, 18 and 30 months.

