As described elsewhere, the CHOICE intervention includes a one-hour initial consultation and follow-up phone calls over three months [20]. The program is designed to have an individualised, structured, case-management approach and is overseen by treating physicians. The development and implementation of the CHOICE program can be divided into four stages (figure 2). Stage one involves the development of modules and tailoring of leaflets to access recommended local services [21]. Stage two is a face-to-face risk factor assessment, lasting approximately one hour in which the patient is assisted to generate a list of their own relevant risk factors. In stage three, patients make guided choices about which risk factors they will address, participate in realistic goal-setting informed by national targets (table 1) [9] and then select management option(s) for lowering risk. The relevant patient information leaflets, described in Stage 1, support these choices. All CHOICE patients participate in the core module for lowering cholesterol as well as up to two choice modules from blood pressure (BP)-lowering, smoking cessation, increased physical activity and nutrition. Patients will have the option to add additional modules on completion of the three-month program. Additional module information will be given over the telephone and written information will be mailed to the patient. Stage four, is telephone follow-up, consisting of approximately four calls of around 10 minutes duration over a three-month period, during which each patient's risk factor(s) goals and strategies are re-evaluated and mutually changed if necessary. CHOICE-*plus *patients will receive additional telephone follow-up over 3 years as previously outlined (figure 1).

**Table 1 T1:** Risk factor targets

**Risk factor**	**National Heart Foundation of Australia targets **[9]
Smoking	Complete cessation
Nutrition	Establish and maintain healthy eating
Alcohol	Low risk alcohol consumption
Physical activity	30 minutes of moderate activity on most days of the week
Healthy weight	Waist measurement
	Male ≤ 94 cm Female ≤ 80 cm
	BMI 18.5–24.9 kg/m^2^
Lipids	LDL < 2.0 mmol/l
	HDL > 1.0 mmol/l
	Triglycerides < 1.5 mmol/l
Blood pressure	Adults ≥ 65 (unless they have diabetes and/or renal insufficiency and/or proteinuria ≥ 0.25 g/day) <140/90 mmHg
	Adults <65 years; adults with diabetes and/or renal insufficiency and/or proteinuria 0.25–1.0 g/day <130/80 mmHg
	Adults with proteinuria >1 g/day <125/75 mmHg

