### Sample size

Given the compelling evidence that lowering TC lowers cardiovascular events, our sample size is calculated based on change in TC. In the previous study with 70/group, we found a 25.5 (SD 1.0) mg/dL (0.66 mmol/L) greater reduction in TC at 12 months in the CHOICE than control group. To demonstrate a difference between CHOICE and CHOICE-*plus *groups, 138 per group in the RCT will give 80% power (2-tailed, P < 0.05) to detect a 0.35 SD effect (13.5 mg/dl (0.35 mmol/L) difference) in TC at 12 months or 3 years. To demonstrate a difference between the control and intervention groups at the single randomized site, 64 patients will be needed in the control group for 80% power. To allow for 20% loss to follow-up and a design effect of up to 1.15 (ICC 0.05) due to cluster sampling, a total of 400 patients will be recruited across the four sites.

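### Read literally, the Group allocation text gives patients later allocated to control a CHOICE session, although controls are to receive no added intervention

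*Protocol article*

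**What the plan says.** Three statements in the protocol article bear on this point.

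- **Group allocation, recruitment step.** "Those who volunteer will have a baseline assessment and an initial face-to-face module selection and goal-setting session (approximately one hour in duration". The subject is everyone who volunteers, at all four sites.
- **Group allocation, randomisation step.** The next timing statement is "After baseline measurements are completed, at three sites, participants will be randomly allocated to one of the two groups", followed by "At the remaining site participants will be randomly allocated to one of three groups", which are control, CHOICE and CHOICE-plus.
- **Interventions.** Controls have conventional care and "will receive no additional intervention as a result of participation in the study". The same section says "the CHOICE intervention includes a one-hour initial consultation and follow-up phone calls over three months". It describes stage two as a face-to-face risk factor assessment of about an hour, and stage three as the point where "patients make guided choices about which risk factors they will address, participate in realistic goal-setting informed by national targets".

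The Sample size section powers a comparison of control with intervention at the single site: "64 patients will be needed in the control group for 80% power".

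**The concern.** The session under Group allocation matches the opening session of CHOICE in content (choosing modules, setting goals), format (face to face) and length (about an hour). It is treatment, not measurement. Attaching it to the baseline assessment for all volunteers, ahead of the sentences on allocation, conflicts with the statement that controls get nothing extra from taking part.

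At stake is the control group at one site, the only randomised comparison of CHOICE with conventional care in this trial. If controls have also reviewed their risk factors, chosen modules and set goals, the comparison reduces largely to the telephone follow-up and is expected to move towards no effect. Risk factor knowledge, a tertiary end point in Table 2, would be directly exposed, because stage two helps patients list their own risk factors. No analysis could restore the contrast once controls had received the session.

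**Working it through.** **1. The passages side by side**

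| Question | Group allocation | Interventions |
|---|---|---|
| Who has the session? | All volunteers, no exception | Described as part of CHOICE |
| What do controls get? | Not addressed separately | Conventional care, nothing added |
| When is randomisation? | After baseline measurements; relation to the session not stated | Not stated |

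Two readings are possible.

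- *Literal reading*: baseline assessment and session for every volunteer, then allocation. This conflicts with the Interventions statement on controls.
- *Reconciling reading*: baseline measurement, then allocation, then the session in the CHOICE arms. This fits the Interventions section and the randomisation sentence, but requires the sentence on volunteers to be restricted in a way it does not state.

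No visible sentence selects the second reading.

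**2. The plan's own figure for the control contrast**

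Inputs from Sample size: 64 controls, 80% power, two-sided 5%. Neither the effect size nor the allocation ratio behind the 64 is given, so the figure cannot strictly be reproduced. It fits a 0.5 SD difference at 1:1:

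n per group = 2(1.96 + 0.84)² / d² = 2 × 7.85 / 0.25 = 62.8, so 63 (64 by the t-test).

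For comparison, at 1:1 the same formula gives 37 per group for 0.66 SD and 129 for 0.35 SD.

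**3. Illustration of dilution**

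Let f be the share of the control contrast lost because controls have had the session. The documents give no value for f. Take 64 v 64 patients analysed:

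power = Φ((1 − f) · d · √(64/2) − 1.96), with √32 = 5.657.

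For d = 0.5:

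| Assumed f | Remaining effect (SD) | Φ argument | Power |
|---|---|---|---|
| 0 | 0.500 | 2.828 − 1.96 = 0.868 | 81% |
| 10% | 0.450 | 2.546 − 1.96 = 0.586 | 72% |
| 25% | 0.375 | 2.121 − 1.96 = 0.161 | 56% |
| 50% | 0.250 | 1.414 − 1.96 = −0.546 | 29% |

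**4. Sensitivity to the unstated inputs**

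- *Ratio.* If controls were compared with both CHOICE arms pooled (64 v 128), power for 0.5 SD would be 90% with no dilution, 69% with 25% and 37% with 50%.
- *Effect size.* The earlier study is reported as "a 25.5 (SD 1.0) mg/dL (0.66 mmol/L) greater reduction in TC at 12 months in the CHOICE than control group". The SD fits mmol/L, in line with the plan's equating of 0.35 SD with 0.35 mmol/L. At 0.66 SD and 64 v 64, power would be 96% with no dilution, 80% with 25% and 46% with 50%.

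The direction is the same throughout. The size depends on f, on the effect assumed and on the ratio.

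**The case against.** The strongest reply is that the protocol never says randomisation follows the session. Its only timing statement ties randomisation to baseline measurements, and concealment is described only in relation to the person who takes consent and does the baseline assessment. Sentence order in a narrative paragraph is not a visit schedule. The Interventions section is specific to each arm and should outweigh a general recruitment sentence, which is in any case accurate for the three sites with no control arm. Figure 1 is not shown and may settle the order.

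Much of this stands. A reader might infer that the passages cannot all be true, or that controls will certainly have had the main part of the intervention before allocation. The documents do not support either: a consistent reading exists, and the Interventions section points towards it. What does not stand is that nothing needs changing. The article states both sides, and nothing visible exempts controls from the session. A site working from this text could deliver it to everyone.

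A reader might also reason that, because the session is about 60 of roughly 100 contact minutes (one hour plus about four 10-minute calls, 60/(60 + 4 × 10) = 60%), it carries 60% of the effect. Contact time is not effect share, and the documents give no such share. Likewise, a fall in power from 96% starts from 0.66 SD, not from the 80% that the plan states for 64 controls.

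**Conclusion.** The point holds as an unresolved conflict in the text. Followed literally, Group allocation would give controls at the three-arm site a session that belongs to CHOICE, and would bias the control contrast there towards no effect. Whether this was intended is doubtful, and the visible text does not decide it.

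The size of the dilution cannot be derived from the documents. The fall from about 81% to about 56% power is an illustration only. It rests on three assumptions: a 0.5 SD effect, 64 v 64 patients analysed, and a 25% loss of contrast. At 0.66 SD the same 25% loss would still leave about 80%.

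The problem is confined to the control comparison at one of four sites. CHOICE versus CHOICE-plus, for which the plan gives 138 per group, is not affected, because both arms receive the session by design.

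**What to change.** Reconcile the Group allocation and Interventions sections. Split the sentence on volunteers so that only consent and baseline measurement precede randomisation. State that the module-selection and goal-setting session follows allocation and is given in the CHOICE and CHOICE-plus arms only. Check that Figure 1 shows the same order.

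The cost is a few words and a fixed order of steps. The small practical downside is that allocation must be obtained between measurement and the session, which needs a prompt allocation service or, failing that, a second contact. Sample size and analysis need no change on this account.
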